		**Modules**			
**Self-report (online)**		**1**	**5**	**9**	**12**
OCD measures	Yale-Brown Obsessive-Compulsive Scale (YBOCS) [44]	x			x
	Obsessive Compulsive Inventory (OCI) [61]	x	x	x	x
	Revised Obsessional Beliefs Questionnaire (OBQ) [62]	x	x	x	x
Psychosocial	Depression, Anxiety, Stress Scale (DASS) [63]	x	x	x	x
	Centre for Epidemiologic Studies Depression Scale (CES-D) [64]	x			
	General Self-Efficacy Scale (GSES) [65]	x			
	Australian Quality of Life Scale (AQoLS) [66]	x			x
	Brief Disability Questionnaire (BDQ) [67]	x			x
	Service Utilisation & Loss of Role Questionnaire (SULRQ) [68]	x			x
Treatment measures	Credibility/Expectancy Questionnaire (CEQ) [69]	x			
	Current Treatments Measure [70]	x			x
	Treatment Evaluation Inventory (TEI) [71]	x			x
	Working Alliance Questionnaire (WAQ) [72]	x			x
	Homework Rating Scale (HSR-II) [73]	x	x	x	x

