### Secondary outcome

Secondary outcomes will be general mental health (depression and anxiety), psychological variables (cognitions related to OCD, self-efficacy), and psychosocial variables (quality of life, functional impairment). We expect that individuals randomised to receive iCBT, compared to matched controls, will demonstrate significantly greater improvements in secondary outcome measures from pre- to post-intervention. We also expect iCBT to be associated with lower service utilisation than the matched control condition.

Demographic and clinical variables, treatment credibility and expectations of treatment, treatment acceptability, working alliance between patient and therapist, and attitudes towards homework tasks will also be assessed. We expect that: a) participants will rate iCBT as more credible and acceptable than the matched control group, but that there will be no differences between groups on working alliance and attitudes towards homework; and b) outcomes will be positively associated with homework completion, but other predictors (e.g. education, gender, age, degree to which other treatments were undertaken) are not expected to contribute to outcomes. Finally, the present study proposes to explore how individual patient characteristics may influence therapeutic outcomes (e.g., demographic variables, functional impairment, treatment readiness, personality, diagnostic/symptom severity, specific symptom presentation, levels of comorbidity, expectancies of treatment credibility).

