### Measures

Outcomes will be assessed via clinician-rated telephone interview at baseline, post-intervention and follow-up. Throughout the intervention and control, participants will self-report secondary outcomes through an online questionnaire embedded within Modules 1, 5, 9 and 12 of each condition. Instruments used to collect data from participants, including primary and secondary outcomes, are listed in Table 1.

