### Data analysis

Exploratory and confirmatory factor analysis will be used to check the psychometric properties of the various scales. Where appropriate, scales will be adjusted and further validation performed to ensure that the resulting scales have internal validity and reliability. The primary analyses will utilise a within and between groups design with two time points (baseline and post-intervention) and two groups (iCBT versus control). Repeated measures analyses will be conducted on follow-up outcomes for the group initially assigned to the iCBT condition. *Clinically significant change* will be based on a combination of reliable reduction in YBOCS scores and post-treatment YBOCS outside the clinical range [74].

Despite randomisation, there are advantages in accounting for potential biases in assignment to treatments [32]. Similarity of baseline characteristics of intervention and control participants will be assessed using appropriate summary statistics and use of multi-level modeling will allow comparison of the iCBT and control conditions in terms of pre-/post changes in primary and secondary outcomes, while controlling for relevant confounds. An intention to treat and completer analyses, and then a longitudinal hierarchical linear model analyses, will be conducted to avoid the need to impute missing data, and baseline data will be examined to analyse probability of attrition bias.

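### Self-efficacy carries a pre-to-post hypothesis between arms, but Table 1 schedules its only instrument, the GSES, at Module 1 alone

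*Protocol article*

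**What the plan says.** Under Secondary outcome, the article lists "psychological variables (cognitions related to OCD, self-efficacy") among the secondary outcomes. It then states that participants randomised to iCBT, compared with matched controls, "will demonstrate significantly greater improvements in secondary outcome measures from pre- to post-intervention". The Data analysis section plans multi-level models for "comparison of the iCBT and control conditions in terms of pre-/post changes in primary and secondary outcomes".

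The Measures section says that "participants will self-report secondary outcomes through an online questionnaire embedded within Modules 1, 5, 9 and 12 of each condition", and gives Table 1 its role: "Instruments used to collect data from participants, including primary and secondary outcomes, are listed in Table 1".

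In the online self-report part of Table 1, the row "General Self-Efficacy Scale (GSES) [65"] has a single mark, under Module 1. The row two lines below the end of that pair of single-mark scales is not needed to see the contrast: the very next row, "Australian Quality of Life Scale (AQoLS) [66"], is marked at Modules 1 and 12.

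**The concern.** A comparison of change between arms needs at least one value before and one value after treatment in each arm. If the GSES is given only at Module 1, the trial announces a test for which it collects no outcome data. Multi-level models can use participants with some missed visits, but they cannot supply an outcome that is never measured after baseline. An analysis plan written later could not repair this either, because the gap lies in data collection.

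At stake is what the trial can report about self-efficacy. Either the hypothesis silently disappears from the results, or it is tested on data whose collection the published schedule does not show. Both would be hard for a reader to interpret.

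**Working it through.** The article gives no figure to reproduce. The check sets the outcome list against the schedule.

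**Step 1. What is needed.** The hypothesis and the planned analysis concern change from before to after treatment, compared between two arms. The minimum is two scheduled occasions per arm.

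**Step 2. What Table 1 schedules for each secondary outcome.**

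| Secondary outcome | Instrument(s) in Table 1 | Before | After |
|---|---|---|---|
| Depression | HRSD (telephone); DASS (online) | yes | yes |
| Anxiety | HRSA (telephone); DASS (online) | yes | yes |
| OCD-related cognitions | OBQ | Module 1 | Module 12 |
| Self-efficacy | GSES | Module 1 | none |
| Quality of life | AQoLS | Module 1 | Module 12 |
| Functional impairment | BDQ | Module 1 | Module 12 |
| Service utilisation | SULRQ | Module 1 | Module 12 |

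Six of the seven outcomes have both values. Self-efficacy has 1 scheduled occasion against the 2 required, and 0 after treatment. With no later value, a change score, a baseline-adjusted final score and a group-by-time term are all inestimable.

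**Step 3. Could another instrument serve?** The telephone part of Table 1 covers demographics, current treatment, diagnosis, OCD severity, depression and anxiety. None of its rows is a self-efficacy measure, and no other online row is identified as one.

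**Step 4. Could the crossover serve?** Controls move on to iCBT after their post-intervention assessment. If they then repeat the Module 1 questionnaires (an assumption; the article does not say so), they would gain a second GSES value. The arm first assigned to iCBT would still have none, so the between-arm comparison would remain impossible.

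**Step 5. Could the marks have been lost when the table was read?** This is unlikely. The GSES row keeps its empty cells for the later modules, and the AQoLS, BDQ and SULRQ rows directly below keep their Module 12 marks.

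**Step 6. How much could still be collected?** The Trial status section reports 179 randomised of 212 planned, so 212 − 179 = 33 remain (33/212 = 15.6%). The article does not say how many of the 179 have passed Module 12. If k of them have not, an addition made at that point could reach at most 33 + k participants:

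- k = 0: at most 33, or about 16 to 17 per arm
- k = 179: at most 212

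Recruitment began in 2010, so values near k = 179 are implausible. Every figure in the range is also reduced by participants who never reach Module 12.

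**The case against.** The strongest reply is that the table, not the data collection, is at fault. The Measures section says that secondary outcomes are self-reported at four modules. Self-efficacy is a secondary outcome, so on that sentence the GSES would be repeated and Table 1 would merely lack a mark. This stands as a real possibility. It does not resolve the matter, because the sentence describes the questionnaire occasions in general: the AQoLS, BDQ and SULRQ have no marks at Modules 5 and 9 either, so the sentence cannot mean that every instrument is given every time.

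A reader might therefore infer that self-efficacy certainly has no post-treatment data and that the loss is beyond repair. The documents do not support that. They show a schedule that contradicts the text, not what was actually collected.

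A second reply is that the point is small. That also stands: it concerns one secondary outcome and leaves the primary outcomes, randomisation and sample size untouched.

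A third is that the GSES was meant only as a predictor. The article does not say so. It places self-efficacy among the secondary outcomes and does not name it among the patient characteristics to be explored as influences on outcome.

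A reader might also extend the criticism to the CES-D, which likewise has a single mark at Module 1. That does not hold. The secondary outcome is depression, not the CES-D score, and depression is measured before and after treatment by the HRSD and the DASS.

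**Conclusion.** The point holds as an inconsistency between the stated hypothesis, the general timing sentence and Table 1. If the table is followed as printed, the self-efficacy hypothesis cannot be tested. The size is one of seven secondary outcomes (six listed constructs plus service utilisation). It should be fixed, but it does not threaten the trial's main conclusion.

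This rests on two readings: that the GSES is the only self-efficacy instrument, as Table 1 indicates, and that the printed marks are those of the published table. Whether post-treatment GSES values exist is not known from the article.

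**What to change.** First establish whether the GSES is collected after treatment.

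- **If it is:** correct Table 1 to show the GSES at Module 12. The cost is one mark in a table.
- **If it is not, and the outcome is to be kept:** add the GSES to the existing Module 12 online form now. State in advance that the result is an exploratory comparison on partial data, since participants already past Module 12 have no post-treatment value and those with values will be mainly later entrants. Report how many in each arm contribute. The cost is one more questionnaire on an existing form, and an answer of limited strength.
- **If it is not, and the outcome is not to be kept:** remove self-efficacy from the secondary outcomes that carry a pre-to-post hypothesis, and describe the GSES as a baseline predictor only. The cost is one edit to the outcome list.

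In each case the Secondary outcome text, the timing sentence in Measures and Table 1 should agree. The CES-D schedule needs no change.

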### Data analysis

Exploratory and confirmatory factor analysis will be used to check the psychometric properties of the various scales. Where appropriate, scales will be adjusted and further validation performed to ensure that the resulting scales have internal validity and reliability. The primary analyses will utilise a within and between groups design with two time points (baseline and post-intervention) and two groups (iCBT versus control). Repeated measures analyses will be conducted on follow-up outcomes for the group initially assigned to the iCBT condition. *Clinically significant change* will be based on a combination of reliable reduction in YBOCS scores and post-treatment YBOCS outside the clinical range [74].

Despite randomisation, there are advantages in accounting for potential biases in assignment to treatments [32]. Similarity of baseline characteristics of intervention and control participants will be assessed using appropriate summary statistics and use of multi-level modeling will allow comparison of the iCBT and control conditions in terms of pre-/post changes in primary and secondary outcomes, while controlling for relevant confounds. An intention to treat and completer analyses, and then a longitudinal hierarchical linear model analyses, will be conducted to avoid the need to impute missing data, and baseline data will be examined to analyse probability of attrition bias.

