### Primary outcome

The primary outcomes will be clinically significant change in obsessive-compulsive symptom scores and diagnostic status. Our primary hypothesis is that individuals in the iCBT and matched control groups will experience reduction in the proportion of diagnosable OCD and significant alleviation of OCD symptoms from pre to post-intervention, with significantly greater improvements in iCBT. It is further anticipated that iCBT outcomes would be maintained at 6-to-12 month follow-up.

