### Sample size calculation

Given previous research showing large effects for online CBT for OCD [43, 45], we expect a large effect for iCBT (i.e., 33% achieving clinically significant change in YBOCS scores; Cohen’s d of approximately 1.0). Progressive relaxation training (PRT) will be the active attention control [51]. PRT has demonstrated inconsistent effectiveness in treating OCD with studies indicating low [52] and high efficacy [53]. Given this, we anticipate a moderate effect size for this group (i.e., 15% achieving clinically significant change in YBOCS scores; Cohen’s d approximately 0.5). Therefore, 88 individuals per intervention group will be sufficient to detect a difference in effects between iCBT and control at post-intervention, assuming significance is set at 5% (α = 0.05) power at 80% and a standard deviation of 5 for the distribution of mean change. We include an additional 20% (N = 18 per group) to allow for attrition and potential effects of various extraneous influences, such as protocol adherence; 106 participants per group will be required (total = 212).

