**Table 1 Tab1:** **Instruments used for data collection**

Measurement tools/questions		Time point			
Clinician administered (telephone)		Baseline	Post-treat		Follow-up
Demographics	Age, gender, postcode, family characteristics, religion, education, general medical history	x			
Current treatment	Current physiological & psychological treatment	x	x		x
Diagnosis	Structured Clinical Interview for DSM-IV Axis I Disorders - Clinician Version (SCID-IV) [50]	x	x		x
OCD severity	Yale-Brown Obsessive-Compulsive Scale (YBOCS) [44]	x	x		x
	Obsessive-Compulsive Inventory (OCI) [57]	x	x		x
	Clinical Global Improvement Scale (CGI) [58]	x	x		x
Mental health	Hamilton Rating Scale for Depression (HRSD) [59]	x	x		X
	Hamilton Rating Scale for Anxiety (HRSA) [60]	x	x		x

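### The plan allows outcome scales to be re-scored after factor analysis of trial data, with no outcome exempt and no limit to baseline or allocation-blind data

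*Protocol article*

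**What the plan says.** The Data analysis section of the protocol article opens with a psychometric step: "Exploratory and confirmatory factor analysis will be used to check the psychometric properties of the various scales". The next sentence says what follows from it: "Where appropriate, scales will be adjusted and further validation performed to ensure that the resulting scales have internal validity and reliability".

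Later in the same paragraph, clinically significant change is defined as a combination of "reliable reduction in YBOCS scores and post-treatment YBOCS outside the clinical range", with a citation for the method and no printed cut-off.

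Three other places bear on the point:

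- **Primary outcome section:** "The primary outcomes will be clinically significant change in obsessive-compulsive symptom scores and diagnostic status".
- **Table 1:** the YBOCS is listed both as a clinician-administered measure (baseline, post-treatment, follow-up) and as an online self-report (Modules 1 and 12). The other multi-item scales for obsessional beliefs, mood, quality of life and disability are listed with it, each with a reference.
- **Sample size calculation section:** the planning rates are "33% achieving clinically significant change in YBOCS scores" for iCBT and "15% achieving clinically significant change in YBOCS scores" for the control.

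The article sets no criterion for adjusting a scale. It does not say which time points feed the factor analyses or whether the analysts will know allocation, and it does not commit to keeping the original scoring for the trial comparisons.

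**The concern.** This is a stated rule that makes scoring depend on the data; it is not a detail left for later. An analysis plan that fixed published scoring for all outcomes would have to depart from it.

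Three things are at stake.

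1. **Pre-specification.** If items can be dropped, moved between subscales or re-weighted after the data are seen, the outcome variable itself is not fixed in advance. This matters most for the secondary outcomes, nearly all of which are multi-item scales.
2. **Validity of the primary responder outcome.** Reliable change and the clinical range belong to a scale scored in a particular way. They do not carry over to a scale with other items or weights.
3. **Comparability.** The Background compares iCBT with earlier trials on the YBOCS, including 60% against 6% with clinically significant change in the largest. A re-scored YBOCS could not be set directly beside those results unless the original scoring were also reported.

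**Working it through.** The point is mainly one of logic, but one piece of arithmetic shows how closely the trial's size is tied to the YBOCS as scored.

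**Step 1. Reproduce the planned sample size.**

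Inputs from the Sample size calculation section: p1 = 0.33, p2 = 0.15, α = 0.05, power 80%. Two-sided testing is an assumption, since the article does not state sidedness. The pooled-variance formula, without continuity correction, is

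n = [z(α/2)·√(2·p̄·q̄) + z(β)·√(p1·q1 + p2·q2)]² / (p1 − p2)²

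- p̄ = (0.33 + 0.15)/2 = 0.24, so 2·p̄·q̄ = 2 × 0.24 × 0.76 = 0.3648, with square root 0.6040.
- p1·q1 + p2·q2 = 0.2211 + 0.1275 = 0.3486, with square root 0.5904.
- Numerator: (1.960 × 0.6040 + 0.842 × 0.5904)² = (1.184 + 0.497)² ≈ 2.825.
- Denominator: 0.18² = 0.0324.
- n ≈ 87.2, rounded up to **88 per group**, as stated. Power at 88 is 80.4%.

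Adding 20% gives 88 × 1.2 = 105.6, rounded to 106, or 212 in total. The plan's figure therefore rests on the binary YBOCS responder outcome. A comparison of two means with a standardised difference of 0.5 (1.0 minus 0.5) would need 63 per group, so the trial was not sized on a mean difference.

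**Step 2. Set the two rules in the Data analysis section side by side.**

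| Rule | Scope | What it needs |
|---|---|---|
| Adjust scales after factor analysis | All scales, none exempt | Freedom to change the scoring |
| Clinically significant change | YBOCS | A fixed scoring, because its criteria refer to that scoring |

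In its usual form, the reliable-change threshold is z × SD × √(2(1 − r)), where SD and the reliability r are those of the scale as scored. The article cites a method without printing the formula, so this form is an assumption. The clinical range is a threshold on the scale's score. Removing or re-weighting items changes SD, r and the range of the score, so both criteria would have to be derived again. The two rules conflict if the first is applied to the YBOCS, and the article does not say which prevails.

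**Step 3. Ask when data-driven scoring would bias the comparison.**

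- *Scoring fixed on pooled baseline data:* the data precede any treatment effect, so the choice cannot favour an arm.
- *Scoring fixed on post-treatment data pooled over arms, without using allocation:* if treatment affects no item, arm labels are unrelated to the item data, and the between-arm test keeps its size. If there is a treatment effect, the choice can still alter what is being estimated.
- *Scoring chosen with post-treatment data and knowledge of allocation:* items can be kept or dropped in view of the result, and the comparison can be biased.

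The text permits all three and selects none.

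**Step 4. See how the responder rates drive power.**

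The rates here are assumed for illustration and do not predict what re-scoring would do. At 88 per group, power is 66.6% for 30% against 15%, 62.8% for 33% against 18%, and 55.6% for 28% against 15%. The planned 80% holds only for the definition on which 33% and 15% were set.

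**The case against.** The best defence is that the specific rule governs the YBOCS and the general sentence covers everything else. Adjustment is conditional, the article never says the YBOCS will be altered, and both its responder definition and its sample size assume the scale as it stands. Some scales in Table 1 measure credibility, alliance or homework, where a psychometric check is reasonable. This largely stands: it makes the YBOCS consequence conditional and puts the weight on the secondary scales. It does not remove the point, because the sentence exempts nothing.

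A second defence is that the stated criterion is internal validity and reliability, not separation between arms. This also stands. A reader might infer that p-values simply lose their nominal error rate; the documents do not support that. As shown above, selection blind to allocation keeps the size of the test when there is no effect. Bias needs a choice informed by allocation, which the text permits but does not describe.

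Two further readings go too far.

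- **An effect in YBOCS points.** A reader might remove an item and compare the shift with the 2.5 points implied by (1.0 − 0.5) × 5. The article does not give the item structure or state a 2.5-point difference, and the trial was not sized on one (63 against 88 per group). A shift in one patient's score is also not comparable with a mean difference between arms.
- **Too few participants for factor analysis.** The article does not say which data or time points would be used, so nothing supports such a statement.

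**Conclusion.** The point holds in a limited form. The plan lets outcome scoring be settled from trial data, without exempting outcomes or restricting the step to baseline or allocation-blind data. The exposure is mainly in the secondary multi-item scales. Bias between arms is possible if the choice uses post-treatment data with knowledge of allocation; it is not inevitable.

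For the YBOCS the consequence is conditional: only if it were adjusted would the criteria for clinically significant change, and the 33% and 15% planning rates, cease to apply. Diagnostic status is assessed by structured interview and is unaffected.

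The size of any bias cannot be derived from the documents. The conclusion assumes that the cited reliable-change and clinical-range criteria relate to the YBOCS as originally scored. The source is cited but its figures are not printed.

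**What to change.** Replace the sentence on adjusting scales with:

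*All outcome scales, including the YBOCS, will be scored by their original published rules for the trial comparisons; factor analyses will be done on pooled baseline data as separate psychometric work, and any modified scale will be used only in sensitivity analyses.*

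For the online questionnaires the earliest administration is Module 1, so the wording should make clear that this is the baseline meant.

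The cost is one sentence. No extra data are needed, the psychometric work is kept, and 88, 106 and 212 stand because no sample size input changes. The Trial status section reports data collection still under way with 179 randomised, so the change can be adopted before any outcome analysis.
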